## Abstract

**Background**: Approximately 3% of women develop posttraumatic stress disorder (PTSD) after giving birth, and 7.5% of pregnant women show a pathological fear of childbirth (FoC). FoC or childbirth-related PTSD during (a subsequent) pregnancy can lead to a request for an elective caesarean section as well as adverse obstetrical and neonatal outcomes. For PTSD in general, and several subtypes of specific phobia, eye movement desensitization and reprocessing (EMDR) therapy has been proven effective, but little is known about the effects of applying EMDR during pregnancy.

**Objective**: To describe the protocol of the OptiMUM-study. The main aim of the study is to determine whether EMDR therapy is an effective and safe treatment for pregnant women with childbirth-related PTSD or FoC. In addition, the cost-effectiveness of this approach will be analysed.

**Method**: The single-blind OptiMUM-study consists of two two-armed randomized controlled trials (RCTs) with overlapping design. In several hospitals and community midwifery practices in Amsterdam, the Netherlands, all eligible pregnant women with a gestational age between eight and 20 weeks will be administered the Wijma delivery expectations questionnaire (WDEQ) to asses FoC. Multiparous women will also receive the PTSD checklist for DSM-5 (PCL-5) to screen for possible PTSD. The clinician administered PTSD scale (CAPS-5) will be used for assessing PTSD according to DSM-5 in women scoring above the PCL-5 cut-off value. Fifty women with childbirth-related PTSD and 120 women with FoC will be randomly allocated to either EMDR therapy carried out by a psychologist or care-as-usual. Women currently undergoing psychological treatment or women younger than 18 years will not be included. Primary outcome measures are severity of childbirth-related PTSD or FoC symptoms. Secondary outcomes are percentage of PTSD diagnoses, percentage caesarean sections, subjective childbirth experience, obstetrical and neonatal complications, and health care costs.

**Results**: The results are meant to provide more insight about the safety and possible effectiveness of EMDR therapy during pregnancy for women with PTSD or FoC.

**Conclusion**: This study is the first RCT studying efficacy and safety of EMDR in pregnant women with PTSD after childbirth or Fear of Childbirth.

## Posttraumatic stress disorder after childbirth, and fear of childbirth

1. 

Although pregnancy and childbirth are supposed to be joyful times, 25% of pregnant women report having psychological problems (Vesga-López et al., 2008). Research indicates that up to 43% of women experience childbirth as traumatic (Alcorn, O’Donovan, Patrick, Creedy, & Devilly, 2010), and it is estimated that 3% of women will develop posttraumatic stress disorder (PTSD) following childbirth (Grekin & O’Hara, 2014). The main symptoms of PTSD, according to DSM-5, are re-experiencing, avoidance and numbing, negative cognitions and mood, and hyperarousal. These symptoms last more than one month and result in significant dysfunction (American Psychiatric Association, 2013). By definition, PTSD after previous childbirth refers to PTSD with childbirth itself being the index trauma. The distinction with non-childbirth related PTSD that is ongoing or retriggered in the postpartum period is not always made correctly (Grekin & O’Hara, 2014). PTSD following other traumatic events is beyond the scope of this study; however, a history of trauma or psychiatric disorders such as PTSD are risk factors for childbirth-related PTSD. Childbirth-related PTSD can occur in the absence of medical complications, but prevalence has been found to be higher among women with complicated pregnancies (Ayers, Bond, Bertullies, & Wijma, 2016). For example, it appears that 14% of women with preterm birth due to preeclampsia or premature preterm rupture of membranes develop PTSD (Stramrood et al., 2011). Posttraumatic stress symptoms after childbirth are not always self-limiting, leading to a chronic disorder (Söderquist, Wijma, & Wijma, 2006). Because the prospect of giving birth may trigger both memories of a previous distressing delivery as well as traumatic events such as sexual violence or previous medical trauma, pregnancy can be accompanied by severe childbirth-related anxiety and a disproportional fear of the upcoming delivery. In addition, avoidance symptoms of PTSD often manifest themselves as avoiding future pregnancy, avoiding prenatal care in a subsequent pregnancy, or demanding an elective caesarean section (Fuglenes, Aas, Botten, Øian, & Kristiansen, 2011; Gottvall & Waldenström, 2002). Moreover, (psychotraumatic) stress during pregnancy appears to be related to negative outcomes for the mother and the foetus (Alder, Fink, Bitzer, Hösli, & Holzgreve, 2007; Seng, Low, Sperlich, Ronis, & Liberzon, 2011; Seng et al., 2001), such as preterm birth (Shaw et al., 2014; Yonkers et al., 2014).

Women who are pregnant for the first time may also experience anxiety symptoms during pregnancy. Overall, about 7.5% of pregnant women experience a pathological fear of childbirth (FoC) (Adams, Eberhard-Gran, & Eskild, 2012; Söderquist, Wijma, Thorbert, & Wijma, 2009). FoC has been found in both nulliparous women who have not experienced childbirth before (primary FoC), as well as in multiparous women (women with a previous birth, whether one or more) in whom a negative or traumatic previous childbirth experience often plays a role (secondary FoC) (Hofberg & Ward, 2003; Størksen, Garthus-Niegel, Vangen, & Eberhard-Gran, 2013). Therefore, it is to be expected that (subclinical) PTSD is accompanied by FoC. FoC appears to be more common in nulliparous women compared to multiparous women (Rouhe, Salmela-Aro, Halmesmäki, & Saisto, 2009). Several studies found that the concept of FoC is multifaceted, including – but not limited to – fear of pain, the baby dying or being handicapped, loneliness, lack of support, or being concerned, or embarrassed about, one’s own appearance while giving birth (Garthus-Niegel, Størksen, Torgersen, Von Soest, & Eberhard-Gran, 2011; Huizink, Mulder, Robies De Medina, Visser, & Buitelaar, 2004). Women with FoC may attempt to avoid pregnancy or even decide to terminate the pregnancy, or request (and receive) a caesarean section (Raïsanen et al., 2014; Størksen, Garthus-Niegel, Adams, Vangen, & Eberhard-Gran, 2015). Moreover, FoC has been found to be associated with increased risk of emergency caesarean section (Ryding, Wijma, Wijma, & Rydhström, 1998), and a sixfold increased risk of PTSD following childbirth (Söderquist et al., 2009).

Prevalence rates of women avoiding pregnancy because of posttraumatic stress symptoms after previous childbirth or FoC are unknown. Avoidance symptoms can include avoiding conversations with healthcare providers about childbirth-related mental health problems, such that even women with the most severe symptoms might not be noticed. Awareness among healthcare providers and women themselves, and an available effective treatment may help to improve quality of life for them and their partners.

## Therapeutic attitudes and practice

2. 

### Fear of childbirth

2.1. 

Related to FoC, a small number of intervention studies have been published, of which a few are controlled trials, and only three were randomized controlled trials (RCT) (Rouhe et al., 2015a; Saisto, Salmela-Aro, Nurmi, Könönen, & Halmesmäki, 2001; Toohill et al., 2014). In 2001, 176 pregnant women were randomized between conventional and intensive therapy (Saisto et al., 2001). Conventional therapy included routine obstetric appointments, standard distribution of written information about pain relief and pros and cons of vaginal delivery versus caesarean section. In the intensive therapy group, appointments were combined with cognitive therapy, and additive informative appointments were recommended. In the intensive therapy group, birth concerns and anxiety were more reduced compared to the conventional group, and labour duration was shorter (mean ± standard deviation; 6.8 ± 3.8 h, compared to the conventional group 8.5 ± 4.8 h, *p* *= *0.04). In both groups the amount of requests for elective caesarean was decreased with no difference between the groups. In a randomized controlled trial among nulliparae with severe FoC, participating in group psycho-education in combination with relaxation, exercises resulted in a more positive childbirth experience (36.1% versus 22.8%, *p* = 0.04), and decreased postpartum depressive symptoms (mean sum score 6.4 ± 5.4 versus 8.0 ± 5.9, *p* = 0.04) (Rouhe et al., 2013, 2015a). The number of uncomplicated vaginal deliveries was significantly higher among women in the intervention group than among the controls (63.4% versus 47.5%, *p* < 0.01), who received care by community nurses and were referred if considered necessary. Because complications lead to more medical costs, a greater number of uncomplicated deliveries reduced medical costs in the intervention group, resulting in group psycho-education being cost-neutral (Rouhe et al., 2015b). In another RCT a telephone psycho-education counselling intervention offered by midwives for 189 pregnant women with FoC was found to be significantly more effective regarding the reduction of childbirth fear levels than care-as-usual (CAU) (clinically meaningful improvement in FoC in 49% versus 26%, *p* = 0.002) (Toohill et al., 2014). A non-randomized controlled trial among 106 pregnant women showed that women who received counselling for FoC by a team of specialized midwives were satisfied with the counselling they received during their pregnancy (Ryding, Persson, Onell, & Kvist, 2003). However, postpartum these women also indicated having had significantly more negative delivery experience compared to the control group (44.3 ± 20.5 versus 29.7 ± 17.4, *p* < 0.01). They also reported posttraumatic stress symptoms more frequently than a matched sample of women from the general parturient population (19% versus 2%). In conclusion, treatment of FoC can lead to a reduction in anxiety, shorter labour duration, and a greater likelihood of uncomplicated vaginal childbirth. Results about the impact of treatment of FoC on childbirth experience are contradictory, and negative effects on posttraumatic stress symptoms have been described (Ryding et al., 2003). However, the amount of previous results, and in specific RCTs, is scarce.

A disproportionate FoC with a level of symptoms meeting the DSM-5 criteria for specific phobia is often referred to as tocophobia (American Psychiatric Association, 2013). Cognitive behavioural therapy, particularly *in vivo* exposure, is generally considered to be the treatment of choice for specific phobias (Barlow, Allen, & Basden, 2007; Wolitzky-Taylor, Horowitz, Powers, & Telch, 2008). However, because *in vivo* exposure is hardly possible for women with FoC, and the fact that EMDR therapy has been found to be effective for a wide variety of specific phobia subtypes (de Jongh, Holmshaw, Carswell, & Van Wijk, 2011; de Jongh, Ten Broeke, & Renssen, 1999; Doering, Ohlmeier, de Jongh, Hofmann, & Bisping, 2013), this may be a promising alternative. Thus far, controlled studies using EMDR therapy among pregnant women with FoC are lacking.

### Posttraumatic stress disorder after childbirth

2.2. 

Since EMDR therapy can be used to treat PTSD resulting from a wide range of traumatic events, it is unlikely that the effectiveness would differ when the traumatic event is childbirth. There are some indications that EMDR therapy is experienced as less intensive than prolonged exposure therapy by the patients, with patients being distracted during therapy; and that there is a faster reduction in symptoms compared to other treatments (Ho & Lee, 2012; Nijdam, Gersons, Reitsma, de Jongh, & Olff, 2012). However, research about treating PTSD following childbirth is limited to some small uncontrolled trials (Lapp, Agbokou, Peretti, & Ferreri, 2010), and even less is known about the benefits and risks of treatment during subsequent pregnancy. Only two small, uncontrolled studies with respectively four women (of which one pregnant) (Sandström, Wiberg, Wikman, Willman, & Högberg, 2008), and three pregnant women (Stramrood et al., 2012) provide some preliminary support for the notion that EMDR therapy can be safe and effective for PTSD following childbirth. A pilot study with four women (of which one pregnant), who fulfilled DSM-IV criteria for PTSD, received an unknown number of EMDR therapy sessions (Sandström et al., 2008). Posttraumatic stress symptoms were reduced (mean score TES 52.7 before, 33.5 after treatment, 22.7 at follow-up), and two participants who completed the follow-up measurements no longer fulfilled the DSM-IV criteria for PTSD after treatment. In a case series three pregnant women with PTSD-symptoms received one or two EMDR therapy sessions followed by a closing session or another three sessions of EMDR therapy for different distressing events (Stramrood et al., 2012). It was found that despite several medical complications, their PTSD symptoms decreased, confidence in the upcoming delivery improved, and that they evaluated their subsequent delivery experience positively. In conclusion, preliminary results show that treatment of childbirth-related PTSD during subsequent pregnancy using EMDR can lead to a reduction in symptoms. Randomized research with validated questionnaires is needed.

Yet, it should be noted that the fact that patients are still continuously confronted with the prospect of the upcoming and inevitable delivery might complicate the condition and treatment. This could easily lead to clinicians being reluctant to offer any treatment at all. In addition, clinicians might be afraid that trauma-focused therapy during pregnancy could provoke a stress response with negative effects on the mother or the foetus. On the other hand, it could be argued that untreated PTSD results in a continuously overactive stress system, which may lead to complications during pregnancy. Furthermore, PTSD is known to have a potentially negative influence on mother–child bonding and the relationship of the mother with her partner (Ayers, Eagle, & Waring, 2006).

## Objectives

3. 

Our main objective is to assess the safety and efficacy of EMDR therapy for pregnant women with PTSD after previous childbirth or FoC. The following hypotheses are tested:

### Posttraumatic stress disorder

3.1. 

Within the treatment group we expect a significant reduction of the severity of PTSD symptoms and percentage of PTSD diagnoses present following EMDR therapy. We expect a significantly larger reduction in PTSD symptom severity and a significantly lower percentage of PTSD diagnoses in the treatment group after completion of the EMDR sessions, compared to the CAU group. Furthermore, we predict a significantly lower percentage of caesarean sections (both elective and unplanned), a significantly more positive childbirth experience, and significantly lower health care costs in the treatment group.

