### Fear of childbirth

3.2. 

Within the treatment group we expect a significant reduction in FoC symptoms following EMDR therapy, a significantly larger reduction in FoC symptoms, a significantly lower percentage of caesarean sections (elective and unplanned), lower health care costs, and a more positive childbirth experience in the treatment group, as compared to the CAU group.

Not least importantly, in both arms we do not predict EMDR therapy to lead to significantly more obstetric or neonatal complications than CAU.

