### Procedure

4.4. 

Women with a gestational age between eight and 20 weeks, regardless of parity, who score above the cut-off score of the Wijma delivery expectations questionnaire (WDEQ-A) at time of screening will be invited for a clinical interview (see Figure 2). In case of multiparity, the PTSD checklist for DSM-5 (PCL-5) is administered at time of screening in addition.

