**Figure 2. F0002:**
[figure not shown]
Study design.

During the clinical interview, traumatic events are explored in all women with the life events checklist (LEC-5). If appropriate, subsequently the clinician administered PTSD scale (CAPS) will be administered to diagnose PTSD (childbirth related, or not). In case of several traumatic events, the CAPS will be administered for each event separately. A pregnant woman is eligible for randomization for PTSD when a PTSD diagnosis can be obtained using the CAPS, with previous childbirth being the index trauma. PTSD with index trauma other than childbirth will be registered and analysed as co-existing psychiatric disorder. When informed consent is obtained, computer-assisted randomization will take place to allocate participants to either EMDR therapy or CAU. If the woman does not meet the criteria for PTSD after previous childbirth, but does score above cut-off on the WDEQ-A, she is eligible to be randomized for FoC (Figure 1). Measurements of (PTSD and/or FoC) symptoms take place between sessions (with childbirth being the index event of the PSS-SR questionnaire): at the start of each therapy session, or in case of CAU, measurements are done two, four and six weeks after randomization by email. Post-treatment antepartum measurement takes place at about 32–34 weeks of gestational age by a blinded assessor. If there is unblinding during the interview, another assessor will finish the interview. Final follow-up takes place two to three months after childbirth. Perinatal healthcare providers are semi-blinded: randomization results are not sent to the professionals, but if a pregnant woman would like to share information with her healthcare provider it is not prohibited.

A limitation for recruitment until 20 weeks of gestation has been chosen to ensure that there is enough time for planning an interview, arranging for therapy logistics, and for scheduling three therapy sessions before post-treatment sessions will take place around 32–34 weeks of gestation.

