#### Wijma delivery expectations/experiences questionnaire (WDEQ-A/B) (Wijma, Wijma, & Zar, 1998)

4.5.8 

The WDEQ is a 33-item self-report questionnaire assessing FoC during pregnancy (version A), and after delivery (version B) in terms of the woman’s cognitive appraisal of childbirth. It was designed as a monofactorial scale, all 33 items being scored on a six-point scale leading to a sum score between 0 and 165, with higher score equalling more FoC. The WDEQ can be dichotomized to conclude if there is FoC or not (cut-off ≥85). Internal consistency is found to be high (≥0.87) (Wijma et al., 1998).

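### Sections 3.1 and 3.2 list a significant fall within the EMDR arm alone as a tested hypothesis, although selection on the baseline measure makes such a result likely without any treatment effect

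*Protocol article*

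**What the plan says.** Section 3 (Objectives) introduces its list with "The following hypotheses are tested". The first item for PTSD in 3.1 concerns the EMDR arm alone: "Within the treatment group we expect a significant reduction of the severity of PTSD symptoms and percentage of PTSD diagnoses present following EMDR therapy". The randomised comparison follows as a separate statement: "We expect a significantly larger reduction in PTSD symptom severity and a significantly lower percentage of PTSD diagnoses in the treatment group". Section 3.2 opens in the same way for FoC: "Within the treatment group we expect a significant reduction in FoC symptoms following EMDR therapy".

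Entry depends on the measure that is later the outcome. For PTSD, section 4.4 states: "A pregnant woman is eligible for randomization for PTSD when a PTSD diagnosis can be obtained using the CAPS". For FoC, a woman without childbirth-related PTSD qualifies if she "but does score above cut-off on the WDEQ-A, she is eligible to be randomized for FoC". The threshold is in 4.5.8: "The WDEQ can be dichotomized to conclude if there is FoC or not (cut-off ≥85". Table 1 schedules the WDEQ-A at screening and not at t0, and the CAPS at t0 and t1.

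Section 4.7 defines the main outcome as the EMDR-CAU difference in CAPS or WDEQ score at follow-up during pregnancy. Section 4.8 plans a linear mixed model comparing the arms with baseline as covariate. It adds Cohen's d based on change from baseline, without saying whether that is within or between arms.

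**The concern.** A group chosen because a score is high will, on average, score lower when measured again. In the PTSD trial every woman has the diagnosis at baseline by design, so any woman who no longer meets the criteria at t1 counts as improvement and none can count as worsening. Time and standard care, which section 4.3.2 says may include extra counselling, add to the change. The article itself shows that this is not negligible: in a cited trial of telephone counselling for FoC (section 2.1), 26% of women under usual care had a clinically meaningful improvement.

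A hypothesis that is likely to be confirmed whether or not EMDR works carries little information about EMDR. Once listed as tested, it can be reported as a positive finding beside a randomised comparison that may not be positive. Only the EMDR-CAU contrast is protected by randomisation.

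**Working it through.** **The plan's own figure first.** With one-sided alpha 0.05 and 80% power, n per group = 2(1.645 + 0.842)²/d². For d = 0.8 this is 12.37/0.64 = 19.3, so 20 (21 with the exact t-test). For d = 0.5 it is 12.37/0.25 = 49.5, so 50 (51 with the exact t-test). The stated 21 and 50 are reproduced. They rest on the between-arm difference, so the within-arm hypotheses play no part in the sample size.

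**FoC, no true change.** Inputs:
- Share of women selected: 7.5%, the prevalence of pathological FoC in section 1, used as the upper tail of a normal score (assumption).
- Completers in the EMDR arm: 60 × (1 − 0.20) = 48, from section 4.7.
- Retest correlation r: 0.7 to 0.9 (assumption). The article gives none for the WDEQ or CAPS-5; the only retest figure is 0.74, for the PSS-SR (section 4.5.2).

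Steps, in population SD units:
1. Cut-off c = z(0.925) = 1.440, where the normal density is 0.1416.
2. Mean of the selected tail: 0.1416/0.075 = 1.887.
3. Variance in the tail: 1 + c × 1.887 − 1.887² ≈ 0.155 (SD 0.39).
4. Expected fall on retest: (1 − r) × 1.887.
5. SD of the change: √[(1 − r)² × 0.155 + 1 − r²].
6. Paired t-test, n = 48, two-sided 0.05, non-centrality = √48 × fall/SD.

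| r | Expected fall | SD of change | Fall/SD | Chance of significance |
|---|---|---|---|---|
| 0.7 | 0.57 | 0.72 | 0.78 | over 99% |
| 0.8 | 0.38 | 0.61 | 0.62 | 99% |
| 0.9 | 0.19 | 0.44 | 0.43 | 83% |

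A simulation of the same model at one-sided 0.05 with 50 to 60 women gave 91–95% at r = 0.9 and 68–74% at r = 0.95.

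**PTSD, no true change.** Simulation with the 3% prevalence in section 1 as the selected tail, 20 to 25 women (25 × 0.8 = 20), one-sided 0.05. Severity was tested by paired t-test and diagnoses by exact McNemar. With everyone positive at baseline, five losses of diagnosis suffice for significance (0.5⁵ = 0.031). Ranges cover selection on the CAPS alone and selection after a PCL-5-type screen, which absorbs part of the regression before t0.

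| r | PTSD severity | PTSD diagnoses |
|---|---|---|
| 0.74 | 76–100% | 96–100% |
| 0.8 | 63–98% | 89–100% |
| 0.9 | 36–81% | 51–99% |
| 0.95 | 22–55% | 21–87% |

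The nominal rate is 5% throughout.

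**The case against.** The strongest reply is that the analysis section plans no such test. Section 4.7 defines the main outcome between arms, and 4.8 compares the arms with baseline adjustment and names no paired or McNemar test. This stands, and it limits the point to how the hypotheses are stated. It does not remove the point, because section 3 says that the listed hypotheses are tested.

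Second, EMDR women may have a later pre-treatment score. Section 4.4 has symptoms measured at the start of each session, and Table 1 marks the WDEQ-A between sessions for the EMDR arm. A change counted from session 1 would avoid much of the regression to the mean. This is a fair qualification. However, that score follows randomisation, is not named as baseline, has no WDEQ-A counterpart in the CAU column of Table 1, and would leave natural course and usual care in the estimate.

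Third, the probabilities rest on assumptions. Rising fear as delivery approaches would lower them; spontaneous remission would raise them. This stands too.

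A reader might go on to infer three things that the documents do not support:
- That a significant fall is all but certain for every outcome. For PTSD severity the rate runs from 22% to 100% over r = 0.74 to 0.95, depending on reliability and the effect of prior screening.
- That Cohen's d in 4.8 is a within-arm quantity. The text fits a between-arm difference in change equally well.
- That the sponsor intends to claim efficacy from the within-arm result if the randomised comparison fails. Nothing in the article says so.

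**Conclusion.** The point holds as a defect in the stated hypotheses. A significant fall in the EMDR arm alone is not evidence that EMDR works, because entry is conditioned on the baseline measure. With no true change, the FoC test would be significant in about 83% to over 99% of trials, given normal scores, no drift, 48 completers, two-sided 0.05 and r between 0.7 and 0.9. For PTSD severity and PTSD diagnoses the rate is less certain, but it stays well above 5% over the whole range tried.

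It would be wrong to conclude that the main result is compromised. Regression to the mean is expected to affect both randomised arms alike, so the baseline-adjusted EMDR-CAU comparison is not biased by it. This is a change that should be made; it does not put the trial's main analysis in doubt.

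**What to change.** - In sections 3.1 and 3.2, delete the within-arm significance hypotheses, or label them descriptive: mean change with a confidence interval, no p-value and no efficacy claim.
- State that conclusions on efficacy rest only on the randomised EMDR-CAU contrast.
- In section 4.8, state that Cohen's d is the baseline-adjusted between-arm difference.

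An extra WDEQ-A at t0 as a new baseline covariate is not advised. Recruitment is under way (section 6), so earlier and later women would have different baselines, to repair a comparison that randomisation already protects.

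The cost is wording only. No visit, form or sample size changes.
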